## Statistical methods

### Statistical methods for primary and secondary outcomes {20a}

Processing and evaluation of data include checks for the plausibility of spirometry data and microbiome data. Moreover, descriptive data analysis will be used to check the plausibility of the distribution of data. For evaluating contextual and compositional determinants, low and high levels of outcome data will be used. In addition, potential determinants for each of the outcomes will be explored by linear regression modelling and will be checked for potential adjustment. Within these approaches, different methods of confounder adjustment (general fixed and random mixed models) will be applied for different association patterns of determinants and risk factors and for risk factor-outcome relationships in cases of clustered risk factors. For repeatedly evaluated measures throughout regression models for longitudinal data, such as the generalized estimating equations (GEE) approach may be applied.

To account for the control arm of this interventional study, multilevel statistical models can be used that integrate information on risk factor-outcome relationships on two complementary levels of intervention and non-interventional group. Such multilevel models can take confounding variables fully into account and are well-suited for studying or identifying specific group effects.

### Interim analyses {21b}

The study protocol requires interim data analyses after the screening and wash-in phase. This analysis will be carried out by the data analysis group and has to be understood as a prerequisite for forming both intervention groups.

### Methods for additional analyses (e.g. subgroup analyses) {20b}

Descriptive and explorative analyses for the planned interventions are planned.

### Methods in analysis to handle protocol non-adherence and any statistical methods to handle missing data {20c}

In case of non-adherence, each individual will be contacted immediately and re-invited to follow the intended timeline. If individuals are unable to proceed with study participation, the corresponding data will be excluded from the phase 1 or phase 2 dataset (lost to follow-up).

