### Trial design {8}

The design of this randomized clinical trial is a “waiting control group design”, which compares the immediate intervention group with the delayed intervention group. The latter one will serve as a control group. The intervention cannot be blinded, but the outcome measure (lung function tests) is blinded, because the technician does not know to which group (immediate or delayed intervention) the subject belongs to. Moreover, the absence of any intervention in subjects with gingivitis would be unethical, but an intervention delayed for 4 weeks seems acceptable.

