### Additional consent provisions for collection and use of participant data and biological specimens {26b}

On the consent form, participants will be asked if they agree to the use of their data should they choose to withdraw from the trial. Participants will also be asked for permission for the research team to share relevant data with people from the cooperating universities. This trial does not involve collecting biological specimens for storage.

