#### Concealment mechanism {16b}

In principle, all participants will receive the same preventive measures owing to ethical reasons. Following the allocation of all subjects to one of the intervention groups, each participant will be informed by telephone about the appointment for the phase 2 baseline examination. As the protocol for the two groups—immediate and delayed intervention—cannot be blinded for the study team and participants, no efforts will be made to conceal this information.

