#### Procedure for unblinding if needed {17b}

The design is open-label with only outcome assessors being blinded so unblinding will not occur.

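### Excluding phase 2 data of participants who cannot proceed is a post-randomisation exclusion: the open-label comparison becomes completers-only, with a risk of attrition bias of unknown size and direction

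*Protocol article*

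**What the plan says.** Section {20c} of the protocol article holds its only rule on missing data. It has two steps. Non-adherent participants are pursued first: "In case of non-adherence, each individual will be contacted immediately and re-invited to follow the intended timeline". Those who still cannot continue are treated as lost to follow-up: "If individuals are unable to proceed with study participation, the corresponding data will be excluded from the phase 1 or phase 2 dataset".

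Other sections show where this rule acts:

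- Section {8} sets out the comparison: "The design of this randomized clinical trial is a “waiting control group design”, which compares the immediate intervention group with the delayed intervention group".
- Interim analyses {21b}: the analysis after screening and wash-in is a precondition for forming the two groups. The stage before it, read here as phase 1, therefore precedes allocation.
- Concealment mechanism {16b}: participants are telephoned about the phase 2 baseline visit after they have been allocated. On the group protocols, "no efforts will be made to conceal this information".
- Procedure for unblinding {17b}: "The design is open-label with only outcome assessors being blinded".
- Additional consent provisions {26b}: "participants will be asked if they agree to the use of their data should they choose to withdraw from the trial".
- Statistical methods {20a}: mixed models are planned, and GEE is optional for repeated measures.

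No section names an all-randomised analysis set or a sensitivity analysis for missing outcomes.

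**The concern.** This is a written decision about who enters the primary comparison, not a detail left to a separate analysis plan. A later plan that kept all randomised participants would contradict it.

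In phase 2 the rule acts after allocation, on people who know their arm and can leave even before the phase 2 baseline visit. The arms also ask different things of them: professional cleaning plus 14 days of twice-daily rinsing in one, a 4-week wait in the other. Loss could therefore differ between arms in rate, in its relation to the outcome, or in both. The groups analysed would then no longer be the groups randomised.

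The rule also sits poorly with two of the protocol's own provisions. Section {26b} seeks consent to use data after withdrawal. Section {20a} allows models that can use partial records, but the exclusion removes those records before any model is fitted.

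**Working it through.** **1. The plan's own figure.** Inputs from Sample size {14}: difference 2 − 1 = 1, SD of the pre-post change about 1.7, two-sided alpha 0.05, power 90%.

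n per group = 2 × (1.960 + 1.282)² × SD² / difference² = 2 × 10.51 × 1.7² / 1² = 60.7, so 61. This reproduces the stated 61. With the unrounded SD √3 = 1.732 it is 2 × 10.51 × 3 = 63.04, so 64. The steps below use √3 and the planned 60 per group.

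**2. Formula for the bias.** If a fraction d of an arm is lost and completers exceed dropouts by a mean gap g, the completers' mean exceeds the full arm's mean by d × g. The bias in the difference between arms is therefore d₂g₂ − d₁g₁. With the same gap in both arms it is (d₂ − d₁) × g.

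**3. Numbers put in.** The loss rates and gaps are assumptions, since the document gives none. True effect 0, 60 randomised per group.

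- Equal loss, for example 10% in each arm, and equal gap: (0.10 − 0.10) × g = 0. Type I error stays at 5%.
- 5% versus 15%, gap 0.5 SD: 0.10 × 0.5 × 1.732 = 0.087 units.
- 5% versus 15%, gap 1 SD: 0.10 × 1 × 1.732 = 0.173 units.
- 5% versus 20%, gap 1 SD: 0.15 × 1 × 1.732 = 0.260 units.

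**4. Type I error.** With 5% and 15% lost, 57 and 51 remain, and SE = 1.732 × √(1/57 + 1/51) = 0.334. The two-sided rejection probability is 1 − Φ(1.96 − bias/SE) + Φ(−1.96 − bias/SE).

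- Bias 0.087: bias/SE = 0.26, giving 5.8%.
- Bias 0.173: bias/SE = 0.52, giving 8.1%.
- 5% versus 20% (57 and 48 remain, SE 0.339), bias 0.260: bias/SE = 0.77, giving 11.9%.

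**5. Direction.** If the immediate arm loses more people and dropouts improve less than completers, the effect is overstated. If the waiting arm loses more, or if dropouts improve more, the sign reverses.

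**6. Power.** By the normal approximation with SD √3, power is 88.5% at 60 per group and 85.1% at 54 per group (10% loss in each arm). Most of this fall cannot be charged to the exclusion rule. The power calculation compares pre-post differences, and a participant without a post-treatment value has no difference to analyse under any rule.

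**The case against.** The strongest defence is that the rule does little harm. Non-adherence alone leads to re-invitation, not exclusion. The delay is only 4 weeks, controls receive the same measures later, and the spirometry technician is blinded. A change of about 2% in FVC in young adults without chronic disease is hardly something they would feel and act on. Loss may be small and similar in both arms, and then the bias is negligible. All of this stands as a reason to call the bias a risk. It does not justify a rule that removes randomised participants whatever the pattern of loss.

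Four stronger readings are tempting and are not supported:

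- **That the rule inflates the effect.** Suppose 10% of the immediate arm have zero change and leave, the rest average 2, and controls average 1 with no loss. The randomised difference is 0.9 × 2 + 0.1 × 0 − 1 = 0.8, while completers show 1.0, a 25% overstatement. This case assumes loss in one arm only and dropouts who do worse than the assumed control mean. Nothing in the document supports that pattern over its opposite.
- **That the rule itself costs several points of power.** As shown in the working, the fall comes mainly from missing post-treatment values. How many usable partial records exist depends on the visit flowchart, which is not shown in the text at hand.
- **That {20c} contradicts {26b}.** Consent to use data does not commit the trial to including them in the efficacy analysis. The two fit poorly but do not conflict.
- **That the analysis is per-protocol.** Only those unable to proceed are removed, so it is completers-only.

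**Conclusion.** The point holds for phase 2. A written rule removes randomised participants from an open-label comparison, and no other section restores them. The consequence is a risk of attrition bias whose size and direction cannot be read from the document. Under assumed losses of 5% versus 15% and a completer-dropout gap of 0.5 to 1 SD, the bias is about 0.09 to 0.17 units, or 9% to 17% of the planned difference of 1, and the type I error is about 6% to 8%. With equal loss and an equal gap it is zero. These figures rest on assumed loss rates and gaps, 60 per group and an SD of √3. Phase 1 exclusions may affect generalisability but not the randomised comparison.

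**What to change.** Replace the phase 2 part of the exclusion sentence in {20c}. In order of importance:

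1. Invite participants who stop the intervention to the scheduled follow-up spirometry. An outcome that is collected does not have to be modelled.
2. Analyse all randomised participants in their assigned group, and keep every observed spirometry value where the consent sought under {26b} permits. The mixed models already foreseen in {20a} can use these records.
3. Add one delta-shift (missing-not-at-random) sensitivity analysis. A missing-at-random model alone does not remove outcome-related loss: in the one-arm example under the objection, with only a baseline value for the dropouts, it would still give about 1.0 unless baseline predicts their poorer response.
4. Report losses and their reasons by arm.
5. Present the completers' analysis as supplementary.

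The cost is protocol wording, a little more follow-up effort and modest analysis work. The estimate may move in either direction. The article describes recruitment as still planned, so on this document the change can be made before any outcome data exist.

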### Plans to give access to the full protocol, participant-level data and statistical code {31c}

The datasets analysed during the current study and statistical code are available from the corresponding author upon reasonable request, as is the full protocol.

### Oversight and monitoring

#### Composition of the coordinating centre and trial steering committee {5d}

The role of the trial steering committee is to provide overall supervision for the trial and provide advice to the trial management group at both study centres, data analysts and the sponsor. The administrators will review and implement the study protocol. Furthermore, they supervise the trial management group when it is initiated. The latter one is responsible for the day-to-day running and management of the trial and meets regularly.

#### Composition of the data monitoring committee, its role and reporting structure {21a}

This study uses approved widely used preventive agents, e.g. CHX, or products, e.g. tooth polishing paste, only. Therefore, the potential risk of adverse events is very low and justifies the decision that a data monitoring committee (DMC) is not needed.

#### Adverse event reporting and harms {22}

This study uses only approved widely used preventive agents, e.g. CHX, and therefore, the risk of adverse events can be assessed as very low and justifies the decision that a systematic registration of adverse events is not included in the trial design.

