In addition to the professional tooth cleaning a full-mouth disinfection using a non-alcoholic, CHX-containing mouth rinse is included in the study protocol which has to be applied twice a day over a period of 14 days. Recent studies [3, 15, 49] showed short-term clinical benefits of one-stage full-mouth disinfection, when compared to the standard treatment strategy of consecutive tooth cleaning alone. Here, the mouth rinse may help to enable proper disinfection of the remaining intraoral niches which could not be reached by the dental instruments especially in patients suffering from periodontitis [50]. With respect to gingivitis patients, van Strydonck et al. [64] analysed the available literature in a systematic review and concluded that CHX mouth rinses together with oral hygiene instruction provided a significant reduction in plaque and gingivitis scores. In another more recently published Cochrane review by James et al. [23], the effectiveness of CHX mouth rinse used as an adjunct to mechanical oral hygiene procedures for the control of gingivitis was assessed in more detail. The authors concluded that there is high-quality evidence of a substantial, but short-term reduction in dental plaque formation when CHX mouth rinse was used as an adjunct to mechanical oral hygiene. In case of gingivitis, the data were insufficient to determine the reduction in gingivitis in association with CHX mouth rinse. Nevertheless, after 4 to 6 weeks of use, CHX mouth rinse reduced gingivitis by an odds ratio of 0.21 (95%CI 0.11 to 0.31) compared to placebo, control or no mouth rinse. There is no evidence that one concentration of CHX mouth rinse (0.1%/0.12%/0.2%) is more effective than another [23]. Nevertheless, the CHX effect on the biofilm is dose-dependent, and the optimum CHX dose is considered to be 20 mg twice daily [36] which represents an equivalent of 10 ml of 0.2% CHX mouth rinse [24]. A rinse time of 30 s appears to be effective and acceptable [24].

Rinsing with CHX mouth rinse for 4 weeks or longer may cause harmful extrinsic tooth staining. Therefore, all study subjects will have access to an additional tooth cleaning after finishing the study protocol.

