### Lung function testing by spirometry

Spirometry prior to bronchodilation will be performed in line with ATS/ERS recommendations [40]. Subjects will sit while wearing nose clips, and the EasyOne Worldspirometer (ndd, Zurich, Switzerland) will be used to obtain flow-volume curves. To obtain optimal flow-volume curves, the participants perform at least three, but no more than eight, manoeuvres under the guidance of specifically trained and experienced examiners. All tests will be visually inspected by experienced physicians according to the ATS/ERS acceptability criteria [40]. Spirometric indices will be taken from the manoeuvre with the largest sum of forced expiratory volume in 1 s (FEV_1_) and forced vital capacity (FVC). Further parameters evaluated will be the ratio of FEV_1_ and FVC (FEV_1_/FVC), and the mean flow rate between 25 and 75% of FVC (FEF_25–75_). Standardized *z*-scores of the lung function parameters FEV_1_, FVC, FEV_1_/FVC and FEF_25–75_ will be calculated based on the reference equations for spirometry from the Global Lung Initiative (GLI—http://www.ers-education.org/guidelines/global-lung-function-initiative.aspx, [48]. After completion of baseline spirometry, subjects will inhale bronchodilator medication according to the ATS/ERS recommendations [40]. Two puffs (each 100 µg) of salbutamol will be delivered into a spacer (volumatic) by a metered-dose inhaler, and the participant will be asked to take five slow and deep breaths over 5–10 s for optimal deposition. Spirometry will be repeated 15 min after salbutamol inhalation. This analysis uses post-bronchodilator lung function data. A positive response is defined as an increase by > 12% and > 200 ml in FEV_1_ and/or FVC post-bronchodilation compared to pre-bronchodilation, according to ATS/ERS standards [40].

Specific attention will be paid to the requirement to obtain very precise and reliable lung function data. In addition to strictly following ATS/ERS recommendations, we will reach the goal of high-quality lung function testing by experienced and well-trained study nurses, the additional visual control by a pulmonologist and the repetition of tests for each subject. There is long-standing, well-documented expertise on lung function assessment in the investigators involved in this study.

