## Discussion

This proposed study has several strengths: (1) It is novel, because it includes subjects with mild (and potentially reversible) oral inflammation. (2) It is innovative, because it includes oral sanitization with lung function testing and measurements of the oral microbiome. (3) It has a high public health relevance, because this study examines the potential improvement of lung function in a period of maximum achieved lung function or at least before a major decline of lung function started and has the potential to develop a strategy to counteract against lung diseases in later life. (4) It might add a piece of causality, because of the interventional aspects and mediating effects by the changes of the microbiome. (5) It is a multidisciplinary research which combines expertise on lung physiology and lung function testing with oral health and oral microbiome and epidemiological skills and statistically modelling. (6) It is a cutting-edge project, because it brings together international experts in the field from Norway (PI: [name]), with the potential to extend this interventional study to other countries. (7) It goes beyond a simple observation and hypothesis generation, because this interventional study is a proof of principle.

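### The reason given for not registering adverse events systematically does not cover the salbutamol used for the primary outcome, so the trial will have no systematic harms data to set beside a gain it calls small

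*Protocol article*

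**What the plan says.** The section on adverse event reporting and harms {22} argues in two steps. It first states the premise: "This study uses only approved widely used preventive agents, e.g. CHX, and therefore, the risk of adverse events can be assessed as very low". It then concludes that this "justifies the decision that a systematic registration of adverse events is not included in the trial design". The section on the data monitoring committee {21a} uses the same premise: "the potential risk of adverse events is very low and justifies the decision that a data monitoring committee (DMC) is not needed". Neither section gives an event rate or a source for the risk, and neither mentions the bronchodilator.

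Three other places bear on this:

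- **Salbutamol.** The Outcomes section {12} makes lung function before and after bronchodilation the primary outcome. The spirometry section describes the procedure: two puffs of 100 µg each "of salbutamol will be delivered into a spacer", with the test repeated 15 minutes later.
- **Rinse.** The intervention description {11a} prescribes a chlorhexidine rinse "which has to be applied twice a day over a period of 14 days". It then warns: "Rinsing with CHX mouth rinse for 4 weeks or longer may cause harmful extrinsic tooth staining". It draws a consequence for everyone: "Therefore, all study subjects will have access to an additional tooth cleaning after finishing the study protocol".
- **Use of the result.** The Discussion says the study "has the potential to develop a strategy to counteract against lung diseases in later life", and it also describes a 2% improvement as small in clinical terms. The dissemination section regards an interventional result as closer to a recommendation than an observational one.

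**The concern.** This is a stated design decision with a stated reason, not a detail that a condensed article leaves to another document. The reason can therefore be checked against the rest of the text, and it is incomplete. Salbutamol is a bronchodilator, not a preventive dental agent. It is given to people aged 18 to 30 from whom asthma and other chronic diseases have been excluded, and it serves measurement only. The risk judgement in {22} and {21a} was formed without it.

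What is at stake is interpretation and the safety record, not the FVC comparison. If the trial finds the hoped-for improvement of about 2%, readers will ask what the programme costs participants in unwanted effects. Followed as written, the trial could give no systematic count in either arm, and the gap cannot be filled after the visits are over.

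**Working it through.** **Step 1: does the premise cover every agent used?** The plan gives no event rate, so there is no figure to reproduce. The check is a comparison of sections.

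| Agent or procedure | Where | Covered by the premise in {22} and {21a}? |
|---|---|---|
| Tooth cleaning, polishing paste, fluoride varnish | Intervention description {11a} | Yes |
| Chlorhexidine rinse, 14 days | Intervention description {11a} | Yes, named as the example |
| Salbutamol, two puffs of 100 µg | Outcomes {12}; spirometry section | No |

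The restriction to preventive agents is therefore not accurate for the trial as described.

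**Step 2: how far does the staining passage go?** The warning applies to rinsing for 4 weeks or longer, and the planned course is 14 days, half of 4 weeks. The named harm thus lies outside the planned exposure as the article describes it. Even so, the article offers an extra cleaning to all participants because of it. The passage shows that staining was thought relevant enough to act on but is not to be counted. It does not show that staining is expected at 14 days.

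**Step 3: what would systematic recording deliver?**

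Inputs: 120 participants in total (Abstract, Methods); about 60 per group (Sample size {14}); both groups eventually receive the same measures (Concealment mechanism {16b}); the delayed group waits 4 weeks (Trial design {8}).

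With no events among n people, the exact one-sided 95% upper limit for the risk is 1 − 0.05^(1/n):

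- n = 60 (treated in the randomised comparison): 1 − 0.05^(1/60) = 0.0487, about 4.9%.
- n = 120 (everyone treated and followed): 1 − 0.05^(1/120) = 0.0247, about 2.5%.

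The chance of seeing at least one event is 1 − (1 − p)^n. The article gives no p, so the range below is assumed:

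| Assumed true risk p | n = 60 | n = 120 |
|---|---|---|
| 0.5% | 26% | 45% |
| 1% | 45% | 70% |
| 2% | 70% | 91% |
| 5% | 95% | 99.8% |

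Recording would thus probably reveal effects occurring in a few per cent of participants and could easily miss rarer ones. Without it, neither table nor limit can be produced.

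**Step 4: what can a comparison by arm show?** Up to the 4-week comparison only the immediate group has had the intensified treatment, so counts by arm bear on the oral intervention. Salbutamol is given in both arms, so those counts cannot isolate its effect. Events after inhalation can only be described.

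**The case against.** The other side has a fair case. The choice is disclosed and reasoned, the concept has ethics approval, the dental products are in common use, and participants see dental staff repeatedly, so a problem may well be noticed. The choice leaves the primary comparison untouched. All of this stands, and it limits the weight of the point. It does not repair a premise that omits one of the agents.

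A reader might infer more than the text supports:

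- **That no adverse event will be recorded at all.** The article rules out systematic registration only. It describes no other route, but the full protocol, which is available on request, may deal with spontaneous or serious events.
- **That the staining warning contradicts the low-risk statement.** Step 2 shows why it does not: the durations differ. Salbutamol is the stronger ground.
- **That the trial fails to prove its own low-risk claim, or promises a benefit-harm conclusion.** The risk statement is a prior judgement from approval status, not a result to be shown. No benefit-harm analysis is announced, and the Discussion calls the study a proof of principle.
- **That a data monitoring committee is needed.** Nothing in the article shows this for a small, short trial. The committee section matters here only because it repeats the incomplete premise.
- **That recording would confirm a very low risk with a 2.5% limit.** That limit needs all 120 treated and followed. The randomised comparison gives about 4.9%, and neither value would confirm a risk as very low.

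**Conclusion.** The point holds in a limited form. The decision against systematic registration rests on a premise that does not cover salbutamol, and the article takes an extra measure against staining that it does not plan to count. Followed as written, the trial will have no systematic harms data beside a gain that it describes as small. It should be corrected, but it does not threaten the validity of the FVC comparison.

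What is lost is modest: with no events, an upper limit of about 4.9% for 60 treated or 2.5% for 120 treated, and a comparison by arm for the oral intervention. These figures assume about 60 per group, complete follow-up, and that everyone is asked in the same way. The detection chances rest on assumed risks of 0.5% to 5%, since the article gives none.

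**What to change.** 1. Reconcile {22} and {21a} with the spirometry section, so that the risk statement covers every agent given, including salbutamol.
2. Replace the sentence in {22} that excludes systematic registration with wording to this effect: *At each existing visit, in both arms, dental staff ask one open question about unwanted effects and complete a short checklist that includes tooth staining. Serious events are logged. Counts are reported by arm up to the 4-week comparison and overall after the delayed group has been treated. Events after salbutamol are reported descriptively.*
3. State that the blinded spirometry technician neither asks the questions nor sees the form, because answers about the rinse could reveal the allocation.

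The remaining checklist items are for the investigators to choose; the article names only staining.

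The cost is one form page at visits that already take place and one table in the report. Clinical care, visit schedule, sample size and primary analysis stay as they are. The change has to be in place before data collection; the article describes recruitment as still planned.
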